### Data management

3.2

For each admitted case, a clinical trial electronic case report form (eCRF) completed by the investigators will be used to record and deposit patient data. The collected data will be reviewed by the investigators and handed over to the data administrators for entry and management. To ensure data accuracy, two data administrators will independently perform double entry, followed by computer verification and manual cross-checking. The data will then be handed over to statisticians for blind verification and subsequent statistical analysis. This comprehensive data management process will ensure the integrity and reliability of the data used in the study.

### Data analysis

3.3

#### Analysis of primary endpoints

3.3.1

Primary endpoints will be analyzed according to the intention-to-treat principle. Missing data will be censored at the last known date of patient survival. Sensitivity analysis will be performed based on the per-protocol (PP) principle. The study is intended to assess the noninferiority of the 2-year disease-free survival (DFS) rate in the LRH group compared to the ARH and gasless LRH groups, with a noninferiority limit set at 9%.

The DFS rate will be estimated using Kaplan-Meier curves, while the hazard ratio (HR) and one-sided 97.5% confidence interval (CI) will be calculated using a Cox proportional hazards regression model, confirming the proportional hazard assumption. One-sided 97.5% CIs will be reported for DFS differences and HRs, whereas other CIs will be two-sided 95% CIs unless otherwise specified.

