### Study design

2.1

This prospective, multicenter, open, parallel, randomized controlled study was mainly focused on investigating the prognosis of early-stage cervical cancer patients who underwent surgical treatments with different approaches. Participants are randomly assigned to receive conventional LRH, gasless LRH or ARH (**Figure 1**). The trial will be conducted in the leading center, Obstetrics and Gynecology Hospital of Fudan University, and the other 3 participating centers in China: Shanghai Sixth People’s Hospital, West China Second University Hospital of Sichuan University and Ruijin Hospital Affiliated to Shanghai Jiaotong University School of Medicine. All four hospitals are Class A tertiary hospitals in China equipped with advanced medical technologies, multidisciplinary health care teams, and robust research capabilities, enabling them to offer comprehensive services related to cervical cancer. The study is registered at http://www.chictr.org.cn/(ChiCTR2000035515, Registered 13 August 2020). Recruitment of participants started in November 2020 and the last participant is expected to reach the primary endpoint (2-year follow-up) in November 2025.

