### Endpoints

2.3

The primary endpoint is 2-year disease-free survival (DFS). The secondary endpoints include the 2-year overall survival (OS), 5-year DFS/OS, operation time, intraoperative blood loss, surgery-related complications, and quality of life (QoL). DFS and OS will be defined as the interval from the time of surgery to the time of recurrence or death for any reason, respectively. Recurrence will be diagnosed based on radiographic evidence using the Response Evaluation Criteria in Solid Tumors (RECIST) criteria. The EORTC-QLQ-C30 V3.0 questionnaire will be applied to assess the quality of life (QoL).

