### Randomization

2.4

Randomization will be conducted using an online computer algorithm to allocate the radical hysterectomy (RH) approach at a ratio of 2:1:1 (laparoscopy vs. laparotomy vs. gasless laparoscopy group). The computer algorithm will generate a unique code for each participant and collect basic information in addition to group assignment. Patients and study surgeons will be aware of the treatment assignment.

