### Sample size

3.1

The primary objective of this study was to compare oncologic outcomes among patients undergoing gasless LRH, ARH, and conventional LRH, focusing on 2-year disease-free survival (DFS) as the primary endpoint. Based on previous research results, the estimated 2-year DFS rates for patients undergoing gasless LRH, ARH, and LRH were 97%, 98%, and 96%, respectively. For the study, the noninferiority margin was set at 9%, and there will be a follow-up period of 2 years.

Considering the relative complexity of performing gasless LRH in participant centers compared to leading centers, the sample ratio was set at 2:1:1 (laparoscopy vs. laparotomy vs. gasless laparoscopy group) for statistical analysis, using a one-sided test with a significance level (α) of 0.025. Additionally, a 10% dropout rate, including those lost to follow-up, was assumed for the study. Based on these considerations, the study is estimated to have a statistical power of 97% to detect any survival differences (one-sided test, α=0.025).

In summary, considering the maximum sample size, both the laparotomy group and the gasless laparoscopy group will each require 126 patients, while the laparoscopy group will require 248 patients, resulting in a total of 500 patients needed for the study.

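### DFS and OS are timed from surgery while the primary analysis is called intention-to-treat, so a randomised patient who is never operated on has no time zero and cannot be analysed.

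*Protocol article*

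**What the plan says.** Four statements in the protocol article bear on this.

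- **Time origin (2.3 Endpoints):** "DFS and OS will be defined as the interval from the time of surgery". The clock ends at recurrence or death.
- **Population and handling of gaps (3.3.1 Analysis of primary endpoints):** "Primary endpoints will be analyzed according to the intention-to-treat principle". On incomplete follow-up: "Missing data will be censored at the last known date of patient survival". On robustness: "Sensitivity analysis will be performed based on the per-protocol (PP) principle". The estimates come from Kaplan-Meier curves and a Cox model.
- **Order of events (2.1 Study design):** "Participants are randomly assigned to receive conventional LRH, gasless LRH or ARH". Allocation is to an approach still to be received, so it precedes the operation.
- **Blinding (2.4 Randomization):** "Patients and study surgeons will be aware of the treatment assignment".

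The objective is noninferiority: "The study is intended to assess the noninferiority of the 2-year disease-free survival (DFS) rate in the LRH group", compared with ARH and with gasless LRH, at a 9-point margin.

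**The concern.** An intention-to-treat analysis needs an outcome defined for everyone randomised. Time from surgery is undefined for a patient who is randomised and then has no operation at all. Such a patient cannot be placed on a Kaplan-Meier curve or in a Cox risk set, whatever the analysis is called.

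Non-operation happens after randomisation and with the allocation known, so it may depend on the arm. The article itself gives reasons why patients or surgeons might react differently to each allocation. The Introduction reports that guidelines favour the open approach and that minimally invasive surgery offers quicker recovery. The Discussion concedes that the gasless technique is new and may be harder to perform.

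At stake is whether the primary comparison keeps the protection of randomisation or compares groups selected after it.

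**Working it through.** **1. Does any other statement supply a start date?** Setting the sections side by side:

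- Section 2.3 gives one origin, surgery, and no alternative.
- The censoring rule in 3.3.1 fixes when follow-up ends. It cannot create a beginning.
- The per-protocol sensitivity analysis is narrower than the primary analysis, so it does not bring unoperated patients back.

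Nothing in the document gives these patients a time zero.

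**2. The plan's own figures.** Section 3.1 states that "the estimated 2-year DFS rates for patients undergoing gasless LRH, ARH, and LRH were 97%, 98%, and 96%, respectively", with margin 0.09, one-sided α 0.025, 10% dropout, 126/126/248 patients (ARH / gasless LRH / LRH) and 97% power. After dropout, about 113/113/223 are evaluable.

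With unpooled variance, power = Φ[(0.09 − Δ)/SE − 1.96], where SE = √(p₁(1−p₁)/n₁ + p₂(1−p₂)/n₂).

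- Gasless vs ARH: SE = √(0.0291/113 + 0.0196/113) = 0.0208; (0.09 − 0.01)/0.0208 − 1.96 = 1.89; power 97.1%. In reverse, 97% power needs 113 per arm, and 113/0.9 gives 126, the stated number.
- LRH vs gasless: power 97.1%.
- LRH vs ARH: SE = √(0.0196/113 + 0.0384/223) = 0.0186; (0.09 − 0.02)/0.0186 − 1.96 = 1.81; power 96.4%.

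The 97% is reproduced.

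**3. Is it a power problem?** If a further 2%, 5% or 10% have no surgery and are lost on top of the 10% dropout, LRH vs ARH power is 96.2%, 95.7% or 94.7%. So the issue is not power. It is what is estimated, and whether the estimate is biased.

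**4. How far could the estimate move?** Let u be the share of an arm that is never operated on and q their 2-year DFS. Neither is in the document; both are assumptions. For all randomised patients, arm DFS = (1 − u) × DFS in operated patients + u × q. The planned rates are taken as those of operated patients, so the operated-only ARH minus LRH difference is 98 − 96 = 2.0 points.

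| Assumed unoperated share | Formula for the all-randomised difference | q = 90% | q = 50% | Shift from 2.0 (points) |
|---|---|---|---|---|
| 2% in both arms | 0.98 × 2.0 | 1.96 | 1.96 | 0.04 |
| 5% in both arms | 0.95 × 2.0 | 1.90 | 1.90 | 0.1 |
| 5% ARH only | 2.0 − 0.05 × (98 − q) | 1.6 | −0.4 | 0.4–2.4 down |
| 5% LRH only | 2.0 + 0.05 × (96 − q) | 2.3 | 4.3 | 0.3–2.3 up |
| 10% ARH only | 2.0 − 0.10 × (98 − q) | 1.2 | −2.8 | 0.8–4.8 down |
| 10% LRH only | 2.0 + 0.10 × (96 − q) | 2.6 | 6.6 | 0.6–4.6 up |

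With equal shares and equal q the term in q cancels. With unequal shares the direction depends on the arm. Leaving out unoperated ARH patients makes LRH look worse than in the full randomised comparison; leaving out unoperated LRH patients makes it look better.

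**The case against.** **Exclusion is inferred.** The article nowhere says that unoperated patients are left out; it says intention-to-treat. As a condensed account, it may leave a rule for such patients to the full protocol or analysis plan. The first part is correct. The second does not remove the problem, because the article fixes both the origin and the population, and the two do not fit.

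**The effect is probably small.** Nothing in the document suggests markedly unequal non-operation. Shifts near 5 points need 10% unoperated in one arm, none in the other, and 50% DFS among them. The 10% dropout allowance is also worded more widely than loss to follow-up, so it may already cover these patients. This stands as regards size, though a dropout allowance protects power and does not remove bias.

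**Stronger readings that a reader might infer, and that the document does not support:**

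- *Patients who switch approach, are upstaged on final pathology or have surgery abandoned also lack a time zero.* They have a surgery date. Only patients with no operation are affected.
- *A count of excluded patients set against the event count measures the bias.* The plan implies about 15 events (0.04 × 223 + 0.02 × 113 + 0.03 × 113 = 14.6), and 2–5% of 500 is 10–25 patients. But excluded patients matter only through their outcomes and through imbalance between arms.
- *Crossover or conversion, by diluting differences, is part of this fault.* It arises in any intention-to-treat analysis and is unchanged by moving the origin.
- *Noninferiority must be shown in both the intention-to-treat and per-protocol sets.* That is a debatable decision rule, and giving per-protocol sensitivity status is not an error.

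**Conclusion.** The point holds. Sections 2.3 and 3.3.1 conflict: followed literally, they give an analysis of operated patients under an intention-to-treat label, with an exclusion after open allocation that can differ by arm.

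The size cannot be read from the document. On the assumptions shown, it is negligible (0.1 point or less) for equal shares of 2–5%, and 0.4–2.4 points for 5% unoperated in ARH only, against a planned difference of 2 and a margin of 9. Neither a direction of bias nor a reversed conclusion is established. The case for correction is that the primary endpoint should be defined for everyone randomised, and that the plan's own label requires it.

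**What to change.** - **Section 2.3:** define DFS and OS from the date of randomisation for all randomised patients, analysed in the allocated arm whether or not surgery is done. State how a patient never rendered disease-free is counted in DFS; the new origin alone does not settle this.
- **Section 3.3.1:** keep time from surgery in operated patients as a sensitivity analysis. The planned per-protocol analysis can stay as it is.
- **Timing:** recruitment began in November 2020 and the last 2-year visit is expected in November 2025. Make the change as a dated amendment before outcomes by arm are examined.

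**Cost:** the sample size stays at 500. An amendment is needed, and a few unoperated patients may add events. Section 2.4 does not list the randomisation date among the items the online system collects, so its availability for every patient should be confirmed.

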Standardized postoperative follow-up will be strictly conducted based on the NCCN guideline, with visits scheduled every 3 months for 2 years, every 6 months for the following 3 years, and annually thereafter (**Table S1**). Routine follow-up items will include physical examinations, HPV tests, LCT, ultrasound, enhanced pelvic MRI, PET-CT, and colposcopy when deemed necessary. Moreover, detailed information on complications arising from both surgeries and adjuvant therapy will also be collected during the follow-up period.

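### The primary DFS analysis censors at the last date known alive, so time without any disease assessment counts as disease-free

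*Protocol article*

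**What the plan says.** Section 3.3.1 (Analysis of primary endpoints) gives a single rule for incomplete follow-up: "Missing data will be censored at the last known date of patient survival". The endpoint under that heading is 2-year DFS, estimated by Kaplan-Meier and tested against a 9-point noninferiority margin.

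Section 2.3 (Endpoints) defines the two survival endpoints together: "DFS and OS will be defined as the interval from the time of surgery to the time of recurrence or death for any reason, respectively". However that sentence is parsed, recurrence is an event for DFS. The same section says how it is established: "Recurrence will be diagnosed based on radiographic evidence using the Response Evaluation Criteria in Solid Tumors (RECIST) criteria".

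The follow-up paragraph at the end of section 2.6 (Treatments) plans "visits scheduled every 3 months for 2 years, every 6 months for the following 3 years, and annually thereafter". Its list of examinations ends with "enhanced pelvic MRI, PET-CT, and colposcopy when deemed necessary", and it is unclear how many of the listed items that qualifier covers. Section 3.1 (Sample size) adds that "a 10% dropout rate, including those lost to follow-up, was assumed for the study".

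No section gives a censoring date specific to DFS. The one sensitivity analysis named is per-protocol, and nothing says that it uses a different censoring date.

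**The concern.** The date fixed for the analysis is a vital-status date, while the endpoint needs disease status. Take a patient who stops attending at month 9 and is known only to be alive at month 24. Under the stated rule she stays in the DFS risk set for 15 months in which nobody looked for recurrence. She can add to the denominator but not to the recurrences, so the estimated hazard is too low and DFS too high.

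This happens in every arm, but the arm with more recurrences gains more. If LRH is truly worse than the reference and loses assessments at a similar or higher rate, the observed difference is smaller than the true one. In a noninferiority comparison that is the anti-conservative direction, and the one-sided 0.025 level is no longer held.

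This is not a detail left open for the analysis plan. The article states a specific date, and that date does not match its endpoint.

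**Working it through.** **Inputs from the protocol article.** Assumed 2-year DFS: "the estimated 2-year DFS rates for patients undergoing gasless LRH, ARH, and LRH were 97%, 98%, and 96%, respectively" (3.1). Margin 9 points, one-sided α 0.025, dropout 10%, and 248 LRH, 126 ARH and 126 gasless patients (3.1).

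**Step 1: the plan's own power.** Unpooled noninferiority test of two proportions with 90% of the patients (223.2, 113.4, 113.4):

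power = Φ[(0.09 − Δ)/SE − 1.96], SE = √[p₁(1−p₁)/n₁ + p₂(1−p₂)/n₂]

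- LRH vs ARH: Δ = 0.02, SE = 0.01857, power 0.965
- LRH vs gasless: Δ = 0.01, SE = 0.02070, power 0.972
- gasless vs ARH: Δ = 0.01, SE = 0.02072, power 0.971

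The stated 97% is reproduced. Power and sample size are not in dispute, and the same test is used below.

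**Step 2: model for the censoring rule (assumptions).** Event times are exponential with λ = −ln(S)/24 per month. All DFS events are treated as recurrences. A fraction d = 0.10 of each arm stops disease assessment at a time u uniform on 0–24 months, unrelated to prognosis. These patients stay known alive for a further g months (at most to month 24), and a recurrence after u is not captured. The document does not give g, so a range is shown.

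At time t:

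- patients really under observation: A(t) = e^(−λt)·[(1−d) + d(1 − t/24)]
- patients counted but unobserved: B(t) = d/(24λ)·[e^(−λ·max(0, t−g)) − e^(−λt)]
- Kaplan-Meier target: S_obs = exp(−∫₀²⁴ λA/(A+B) dt)

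With g = 0, B = 0 and S_obs = S, so censoring at the last disease assessment is unbiased under random loss. With g = 24 the expression reduces to

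1 − S_obs = (1−d)(1−S) + d·E, E = 1 − (1−S)/(−ln S).

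**Step 3: the noninferiority boundary against ARH (LRH 89%, ARH 98%), g = 24.**

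- LRH: E = 0.0561; 0.9 × 0.11 + 0.1 × 0.0561 = 0.1046; S_obs = 0.8954
- ARH: E = 0.0100; 0.9 × 0.02 + 0.1 × 0.0100 = 0.0190; S_obs = 0.9810
- difference 0.0856 instead of 0.0900; SE (248 and 126) = 0.02293
- type I error = Φ[(0.0900 − 0.0856)/0.02293 − 1.96] = 0.0385

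Other gaps, by numerical integration:

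| Known alive after last assessment | LRH read as | ARH read as | Difference (points) | One-sided type I error |
|---|---|---|---|---|
| no gap | 89.0% | 98.0% | 9.0 | 0.025 |
| 3 months | 89.1% | 98.0% | 8.9 | 0.028 |
| 6 months | 89.2% | 98.0% | 8.8 | 0.030 |
| 12 months | 89.4% | 98.1% | 8.7 | 0.035 |
| to month 24 (upper case) | 89.5% | 98.1% | 8.6 | 0.039 |

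At the boundary against the gasless arm (88% vs 97%) the upper case gives about 0.037.

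**Step 4: the planned rates (LRH 96%, ARH 98%), g = 24.** LRH reads 96.2%, ARH 98.1%, and the difference is 1.9 points instead of 2.0.

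**Step 5: unequal loss, planned rates, g = 24.** With 15% lost in ARH and 5% in LRH:

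- LRH: 0.95 × 0.04 + 0.05 × 0.0201 = 0.0390
- ARH: 0.85 × 0.02 + 0.15 × 0.0100 = 0.0185
- difference 2.05 points, slightly away from noninferiority

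**The case against.** The strongest reply is that the two dates may nearly coincide. The 10% includes patients lost to follow-up. For a patient who is truly lost, the last date known alive is at or near the last visit. The article describes visits every 3 months and no separate tracing of vital status. If each last contact is a full disease assessment, the bias is zero. This stands, and it is why the result is a range with month 24 marked as an upper case. It does not rescue the wording, because the rule still names the wrong date, and any contact that establishes only survival triggers the error.

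A second reply is that 0.1 point at the planned rates is negligible against a 9-point margin. That also stands. The effect matters near the boundary, where error control is defined.

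Three stronger readings are tempting, and the document supports none of them.

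- *The rule always favours noninferiority.* With equal true rates and equal loss the difference is unbiased, and Step 5 shows the sign can reverse.
- *The rule can decide the trial, since dropouts outnumber events.* Expected dropouts are 24.8 LRH and 12.6 ARH, against planned events of 9.9 (4% of 248) and 2.5 (2% of 126). But with ARH at 98%, 17 LRH events give an upper limit of 4.85 + 1.96 × 2.03 = 8.8 points, and 18 give 5.26 + 1.96 × 2.07 = 9.3. About 8 extra LRH recurrences would have to be hidden, with none hidden in ARH. Under last-assessment censoring they would be equally unseen. That comparison concerns missing data in general.
- *Dropouts with much higher recurrence make the bias large.* If dropouts recur at an assumed five times the rate, true DFS is 94.6%, last-assessment censoring reads 95.3% and the stated rule 95.5%. Of the 0.9-point error, 0.7 comes from informative dropout and survives the correction. The factor of five has no source in the document.

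**Conclusion.** The point holds. The stated censoring date is wrong for DFS, and nothing else in the article corrects it. DFS is overstated in each arm whenever patients are known alive beyond their last disease assessment. The shift is toward noninferiority when LRH is truly worse and its loss of assessment is similar or greater.

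With 10% dropout in each arm, one-sided type I error against ARH lies between 0.025 and 0.039, depending on a gap that the document does not give. At the planned rates the effect is about 0.1 point. These figures rest on exponential event times, uniform and non-informative loss, and no capture of recurrences after the last assessment. The mechanism is certain from the text; its practical size is not. It should be corrected before the primary analysis because it governs the confirmatory endpoint and costs almost nothing, not because the trial's result has been shown to hang on it.

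**What to change.** In section 3.3.1, replace the sentence on missing data with:

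> DFS is censored at the last disease assessment showing no recurrence; OS is censored at the last date known alive.

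This corrects the censoring date only and does not remove bias from informative dropout. A sensitivity analysis for loss to disease follow-up would address that. It is optional and can sit in the statistical analysis plan, so its absence from the article is not a fault.

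The cost is one sentence and slightly wider confidence intervals, because unobserved time no longer counts as follow-up. The dates needed should come from the scheduled follow-up visits.

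### Noninferiority of LRH is decided on the intention-to-treat set, and the per-protocol result has no stated part in the decision, although neither set is reliably conservative here

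*Protocol article*

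**What the plan says.** Section 3.3.1 (Analysis of primary endpoints) assigns the roles of the two analysis sets. The primary set is fixed by "Primary endpoints will be analyzed according to the intention-to-treat principle", and the other by "Sensitivity analysis will be performed based on the per-protocol (PP) principle". The same section states the aim as "noninferiority of the 2-year disease-free survival (DFS) rate in the LRH group compared to the ARH and gasless LRH groups", with a limit of 9%.

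Section 3.1 (Sample size) repeats the margin ("the noninferiority margin was set at 9%, and there will be a follow-up period of 2 years") and gives the design inputs: "the estimated 2-year DFS rates for patients undergoing gasless LRH, ARH, and LRH were 97%, 98%, and 96%, respectively", tested "using a one-sided test with a significance level (α) of 0.025".

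Section 2.4 (Randomization) makes the trial open: "Patients and study surgeons will be aware of the treatment assignment". The article states no expected rate of conversion, refusal or crossover. It gives no rule for the case where the ITT and per-protocol results differ.

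**The concern.** In a superiority trial, patients who receive the other arm's operation usually make the ITT comparison conservative. In a noninferiority trial the same dilution can work the other way: the arms look more alike, and a real deficit is easier to miss. A per-protocol analysis is the usual counterweight, but here it carries no weight in the conclusion.

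The article gives some reason to expect switching. Patients and surgeons know the allocation. The Introduction reports an earlier randomised trial with worse survival after minimally invasive surgery, and guidelines that now favour the open route. Section 3.1 says gasless LRH is harder to deliver outside the leading centre. What is at stake is a safety claim about cancer recurrence, so the role of each analysis set in that claim should be settled before results are known.

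**Working it through.** **Inputs from Section 3.1.** Arms of 248 (LRH), 126 (ARH) and 126 (gasless LRH); 10% dropout; 2-year DFS of 96%, 98% and 97% respectively; margin 0.09; one-sided α 0.025. Evaluable numbers: 248 × 0.9 ≈ 223 and 126 × 0.9 ≈ 113.

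**Formula.** Chance of declaring noninferiority = Φ[(0.09 − D)/SE − 1.96], where D = p_C − p_T (comparator minus tested arm) and SE = √[p_C(1−p_C)/n_C + p_T(1−p_T)/n_T].

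**Step 1: reproduce the plan's 97% power.**
- LRH vs ARH: D = 0.02, SE = √(0.0196/113 + 0.0384/223) = 0.01859, so Φ(3.765 − 1.96) = 96.4%.
- LRH vs gasless LRH: 97.1%.
- Gasless LRH vs ARH: 97.1%. At 97% power this pair needs 113 per arm, or 126 after dividing by 0.9, as stated.

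The stated power therefore reproduces with this formula, which is used below.

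**Step 2: false noninferiority under ITT when switched patients take the outcome of the operation received.** Put the truth on the margin: ARH 98%, LRH 89%. If a fraction c of LRH patients is operated on openly, the LRH rate under ITT is (1−c) × 0.89 + c × 0.98. The values of c are assumptions.

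| c | LRH rate under ITT | D | SE | False noninferiority |
|---|---|---|---|---|
| 0 | 0.8900 | 0.0900 | 0.02475 | 2.5% |
| 2% | 0.8918 | 0.0882 | 0.02462 | 3.0% |
| 5% | 0.8945 | 0.0855 | 0.02443 | 3.8% |
| 10% | 0.8990 | 0.0810 | 0.02410 | 5.6% |

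Binomial simulation (400,000 runs) gave 2.6%, 3.9% and 5.7% at c = 0, 5% and 10%. With switching in both directions the normal approximation gives about 5.4% at 5% each way and 10.4% at 10% each way.

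For LRH vs gasless LRH on the margin (88% vs 97%), if 5% or 10% of gasless patients receive conventional LRH, the figures are 3.6% and 5.0%.

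**Step 3: the opposite case, where converted patients do worse.** Keep the LRH rate under ITT at 89%, but suppose converters have 80% DFS (an assumption). Per-protocol drops them.
- 10% convert: the rest have (0.89 − 0.10 × 0.80)/0.90 = 0.900 with n = 201. D = 0.080, SE = 0.02492, false noninferiority 5.9%.
- 5% convert: (0.89 − 0.05 × 0.80)/0.95 = 0.8947 with n = 212. D = 0.0853, SE = 0.02485, false noninferiority 3.8%.

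ITT stays at 2.5% in both cases, so here per-protocol is the lenient set.

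**Step 4: requiring both sets.** Simulation for the Step 2 setting, with conversion unrelated to prognosis, gives joint false noninferiority of about 2.7% at 5% conversion and 2.9% at 10%, against 3.8% and 5.8% for ITT alone in the same runs. The small excess over 2.5% is approximation error of the test, because the per-protocol contrast there sits exactly on the margin. In the Step 3 setting the joint rate cannot exceed that of ITT.

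**Step 5: power cost.** Removing 10% of each evaluable arm leaves 201 LRH and 102 ARH. SE = √(0.0196/102 + 0.0384/201) = 0.01958, so Φ(3.576 − 1.96) = 94.7%, down from 96.4%. In simulation, when only LRH converters leave the per-protocol set, joint power is about 96% at 5% conversion and 95.5% at 10%.

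**The case against.** The strongest reply has four parts.

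- **Per-protocol is already planned.** Readers will see both results, and ITT as primary with per-protocol as sensitivity is a recognised design. A rule for discordant results could sit in an analysis plan that is not shown. The first part stands: the safeguard is present, though without force. The last does not remove the point, because Section 3.3.1 itself assigns the roles, and that is a stated choice.
- **The direction of bias is assumed.** A reader might infer that switching must push this trial towards noninferiority. The article does not support that. Step 3 shows an effect of similar size the other way if converters have worse prognosis, and per-protocol gives up the protection of randomisation. This stands in full. It argues for requiring both sets, not for replacing one with the other.
- **The size is hypothetical.** A reader might also infer that the error rate of this trial is above 2.5%. No switching rate is given. Section 2.5 asks for at least 50 LRH and 50 ARH cases per surgeon plus video review, and Section 2.2.2 excludes patients with surgical contraindications; both may limit conversion. Open allocation permits crossover but is not evidence of it. This stands too.
- **Conversion may belong to the question.** If the target is a policy of starting with LRH, an operation finished openly is part of that policy, and ITT keeps its 2.5%. The inflated figures refer to the effect of the operation actually received. That is a fair distinction. It applies less to patients who refuse the assigned approach.

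**Conclusion.** The point holds in a limited form. Section 3.3.1 rests the 9-point noninferiority conclusion on ITT and gives per-protocol no stated part in it, so the claim could be made when per-protocol does not exclude the margin. Against ARH, one-way switching of 2% to 10% would raise false noninferiority from 2.5% to between 3.0% and 5.6%. That requires switched patients to take the ARH outcome and the true deficit to be exactly 9 points. Under the alternative assumption of 80% DFS in converters, per-protocol is the lenient set, at 3.8% (5% converting) to 5.9% (10% converting). Neither set is therefore reliably conservative, and the plan should not let either decide alone. No inflation has been shown for this trial. The change is a cheap improvement, not the correction of a demonstrated error.

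**What to change.** Add one sentence to Section 3.3.1: noninferiority of LRH is concluded only if the one-sided 97.5% confidence limit for the difference in 2-year DFS excludes the 9% margin in both the ITT and the per-protocol sets; if the two disagree, noninferiority is not claimed.

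Both analyses are already planned, so the cost is wording plus a small loss of power: for LRH versus ARH, from about 96.4% to about 94.7% if 10% are excluded from per-protocol. The sample size need not change. The joint rule reduces the inflation but does not guarantee exactly 2.5%.
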